#### **8.1.8 Serious Adverse Event Form**

This will collect details of all SAEs are defined and description in Section 10.5.

#### **8.1.9 Mechanistic Study Data Forms**

Data forms pertinent to the assays and analyses being undertaken on the endometrial biopsy and MRI scans taken for the sub-study will be used to standardise data collected.

#### **8.1.10 Liver Function Test Results**

As per the Urgent Safety Measure: LFTs will be performed monthly during the 12 week treatment period for women currently taking UPA. A LFT must also be performed 2-4 weeks after the final dose of UPA. LFTs must include transaminases (ALT and AST). LFT results must be recorded on the UCON trial database.

### **8.2 SOURCE DATA**

For the purposes of the UCON trial, source data comprises of:

- Clinical Assessment and Randomisation Form
- Patient questionnaire and menstrual diary
- Clinical notes
- Blood sample for haemoglobin and oestradiol analysis
- Ultrasound
- Endometrial biopsy sample for standard histopathological analysis.
- End of Study Visit Form

### **8.3 DATA MANAGEMENT**

Data from the Clinical Assessment and Randomisation Form and Endometrial Biopsy Report Form and should be entered on to the secure online UCON database as soon as possible after collection by the research nurse, investigator or histopathologist, who will be allocated personal usernames and passwords that restrict access to participants at their centre. Alternatively, paper forms can be sent to the UCON Trial Office for central input. Patient completed forms will be returned directly to the UCON Trial Office for data entry.

Data validation is built into the online database, so that range, date and logic checks are performed at the point of data entry. Email, text message and letter reminders will be sent to the research nurses or participants for missing data forms, missing data or data inconsistencies.

## **8.4 QUALITY ASSURANCE OF ENDOMETRIAL BIOPSY ASSESSMENTS**

The assessment of endometrial biopsies should be undertaken by a consultant histopathologist with expertise in endometrial analysis. For quality assurance, a second assessment will be undertaken by the lead pathologist for UCON, [name] at the University of Edinburgh. The histopathologist or research nurse should send the screening endometrial biopsy sample slides to [name] for second reading in secure shipping containers (available from the UCON Trial Office upon request).

Slides taken from the samples will be labelled with:

- Trial No.
- Patient Initials
- Slide Number/Accession Number
- Date biopsy taken

and sent for second reading in secure shipping containers which may be provided by the UCON Trial Office upon request.

For the baseline endometrial biopsy, the second assessment in Edinburgh will not be used to confirm eligibility for the trial and therefore slides may be sent in batches.

For the final post-treatment biopsy in the UPA group, a local assessment will be undertaken and the slides sent promptly to Edinburgh. Whilst the local assessment will be noted, the second Edinburgh review of the slides, undertaken without knowledge of the local assessment, will determine the presence or absence of PAEC for the purpose of the trial. Those women with PAECs as confirmed by Edinburgh will be asked to return for endometrial biopsies at 13 weeks, and if necessary 26 weeks after completion of the final UPA course.

All slides will be returned to their originating hospitals after the second assessment.

## **8.5 MECHANISTIC SUB-STUDY**

### **8.5.1 Endometrial tissue function**

An overview of approach to analysis of tissue-specific impacts of UPA on endometrial tissue function are summarised in Table 2 below. The choice of target endpoints has been informed by studies in our own laboratory that have highlighted the impact(s) of progestins, progestin receptor antagonists and receptor modulators (levonorgestrel, mifepristone, asoprisnil) on endometrial tissue function, *examples given but not limited to those end points identified in Table 2* (17-19).

**Table 2: An overview of approach to analysis of tissue-specific impacts of UPA on endometrial tissue function**

| Process                    | Endpoint                                                                                          | Details of analytical method                                                                                                                                     |
|----------------------------|---------------------------------------------------------------------------------------------------|------------------------------------------------------------------------------------------------------------------------------------------------------------------|
| Tissue morphology          | H&E stain histology, number of mitoses and mitochondria                                           | Analysis by expert pathologist
qRT-PCR mitochondrial markers                                                                                                  |
| Vascular morphology        | Endothelial and perivascular cell function/morphology                                             | Double staining for CD31 (endothelial cells) and smooth muscle actin
Masson Trichrome staining for collagen                                                   |
| Regulation of cell number  | Cell proliferation, apoptosis and autophagy                                                       | Immunostaining for Ki67, PH3(proliferation) or cleaved caspase 3, microtubule-associated protein 1 light chain 3 alpha (death/survival), gamma H2AX (senescence) |
| Steroid hormone signalling | Cell-specific pattern of expression of steroid hormone receptors and steroid metabolizing enzymes | Single and double immunostaining for PR, ERalpha, ERbeta, AR, GR                                                                                                 |
| Inflammation               | Immune cell complement and inflammatory mediators                                                 | qRT-PCR IL15.
Immunostaining for CD56, CD68, neutrophil elastase, mast cell tryptase and pan leucocyte marker CD45                                            |
| Pre-malignant change       | Comparison with normal endometrium and endometrial hyperplasia                                    | qRT-PCR, double fluorescent immunohistochemistry PTEN, E-Cadherin, Snail 1, vimentin, PAX2, telomerase (hTERT)                                                   |

### 8.5.2 Uterine and fibroid function

The aim of the MRI sub-study is to investigate the hypothesis that UPA will reduce blood flow and blood volume in the endometrium and myometrium in women with HMB. In particular, dynamic contrast enhanced MRI (DCE-MRI) and high spatial resolution structural MRI will be obtained in a subgroup of 20 women treated with UPA. DCE-MRI, combined with pharmacokinetic modelling, yields quantitative estimates of physiological parameters, including tissue blood flow, blood volume fraction and endothelial permeability, as well as volume fraction of the extracellular extravascular space. Structural MRI provides high resolution images suitable for structural segmentation and radiological evaluation that, when combined with design based stereological analysis (20), yield accurate and precise measurements of uterine and fibroid volume for early assessment of treatment response.

Scanning will be performed at baseline, and at 6 and 12 months following commencement of treatment. Scans will take place during the secretory phase of the menstrual cycle at baseline and in the week prior to the end of the second and third cycles of UPA, weeks 27 and 43 respectively.

Structural images will be evaluated clinically by an experienced radiologist, and stereological analysis performed to determine the volumes of the uterus and of any fibroids. Modern design based stereological methods will measure total volume of endo- and myo-metrial compartments, and

volume, type and location of individual fibroids, with mathematically predicted precision, on high resolution MR images.

Dynamic Contrast Enhanced (DCE)-MRI will be used to measure uterine tissue perfusion. Contrast agent concentration is modelled as exchange between the blood plasma and extracellular interstitial spaces, providing maps of tissue blood flow, blood and interstitial volume fraction and artery to tissue delay (i.e. lag) time. DCE-MRI data will be analysed using the well-established adiabatic approximation to tissue homogeneity (AAHT) model, to generate pharmacokinetic maps of blood flow, blood volume and extracellular extravascular volume fraction; these will be used to extract representative values for endometrium, junctional zone, outer myometrium and fibroid tissue.

Both MRI approaches are novel in the context of SPRM administration, so will be piloted in the first patients, who may require repeat scans with a refined protocol.

## **9 STATISTICS AND DATA ANALYSIS**

### **9.1 SAMPLE SIZE CALCULATION**

#### **9.1.1 RCT**

The trial has been designed to be able to detect a clinically useful difference in MMAS score between the two groups at twelve months with high power. The ECLIPSE Trial, which evaluated the effectiveness of LNG-IUS against Standard treatment for HMB (21) using MMAS as the primary outcome, demonstrated a difference of 13 points between the groups with a standard deviation of 24 points. This difference considered to be clinically meaningful (22) and is equivalent to approximately 0.5 standard deviations. To detect a difference of this size with 90% power ( $p=0.05$ ) would require 86 women in each group (172 in total). To allow for a 20% loss to follow-up or pregnancy, the sample size has been inflated to 220 women in total.

#### **9.1.2 Mechanistic sub-study**

For the mechanistic evaluation 20 samples would give >90% power ( $p=0.05$ ) to detect a change from baseline in for example, PH3 immuno-score, in the endometrium assuming similar effect sizes (>1 standard deviation) as to those seen in previous studies of other PRMs (19).

#### **9.1.3 Anticipated recruitment period**

Recruitment will take place over a minimum of 24 months from at least 5 centres, with a target of 2 patients/centre/month. All centres have large HMB clinics, are experienced in recruiting to RCTs and the BCTU has a track record of completing RCTs in women's health.

### **9.2 PROPOSED ANALYSES - RCT**

The analysis will be by intention to treat. Every attempt will be made to gather data on all women randomised, irrespective of compliance with the treatment protocol. Appropriate baseline characteristics, split by treatment group, will be presented for each outcome. Point estimates, 95% confidence intervals and p-values from two-sided tests will be reported. A full Statistical Analysis

Plan will be drafted prior to any analysis and provided to independent Data Monitoring and Ethics Committee for review.

### **9.2.1 Primary analysis**

A linear regression model will be used to estimate differences in MMAS responses between the two groups at each time point. Baseline score and the minimisation variables (listed in section 5.5.1) will be included in the model as covariates. The statistical significance of the treatment group variable will be determined by an associated chi-squared test.

### **9.2.2 Secondary analysis**

MMAS scores at three and six months follow-up will be analysed as per the primary analysis. Data from the other continuous measures (UFS-QOL, EQ-5D, ICE-CAP, VAS and SAQ) will be analysed in a similar fashion to the MMAS scores. Further exploratory analysis using a repeated measures model will also be used for these continuous measures to examine differences over all time-points. Bleeding diary scores will be converted into categories including the proportion with amenorrhoea ( $=0$ ) and heavy bleeding ( $\geq 100$ ). They will be analysed using relative risks and chi-squared tests. Time from randomisation to surgery (hysterectomy or endometrial ablation) will be analysed by log-rank test with a Cox Proportional Hazard (PH) model also built if the assumptions of proportionality are met. Other outcome measures (Likert responses, Likert ordinal responses, satisfaction) will be analysed using standard methods (tests for trend, absolute and relative risks). Paired t-tests will be used to examine differences within groups over time.

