#### **5.6 RANDOMISATION**

##### **5.6.1 Randomisation Procedures**

**Randomisation for the trial has been suspended until further notice on account of a USM requirement from the MHRA (12th February 2018).**

**[Procedure adopted prior to USM:** Immediately after eligibility has been established, baseline questionnaires have been completed, and once written informed consent has been obtained, the women may be randomised into the trial.

The Birmingham Clinical Trials Unit will provide third part web-based randomisation with telephone back-up. Patients are entered and randomised into the trial by logging into secure online randomisation available at <https://www.trials.bham.ac.uk/UCON>. Each centre and each randomiser will be provided with a unique log-in username and password in order to randomise a patient online. The online randomisation is available 24 hours a day, 7 days a week apart from short periods of scheduled maintenance and occasional network problems. Alternatively, investigators can make one Freephone telephone call (Tel - [name]) to the randomisation service. Telephone randomisations are available Monday-Friday, 09:00-17:00.

Clinical Assessment and Randomisation Forms will be provided to investigators and may be used to collate the necessary information prior to randomisation. All eligibility related questions and data items on the Clinical Assessment and Randomisation Form will need to be answered before a trial number can be given. Only when all eligibility criteria and baseline data items have been provided will a trial number and treatment allocation be given followed by a confirmatory email sent to the randomising investigator, local Principal Investigator, local pharmacist and the research nurse.

A minimisation procedure using a computer based algorithm will be used to avoid chance imbalances in treatment allocation and the following potentially important variables:

Age:  $\leq 35$  yrs or  $> 35$  yrs

BMI:  $\leq 25$  kg/m^2 or  $> 25$  kg/m^2

Presence of any fibroid  $> 2$ cm, as determined by the ultrasound scans

Duration of symptoms:  $< 1$  year or  $\geq 1$  year

Site: Individual Site

Agreement to enter sub-study: Both/ MRI only/ Biopsy Only/ Neither and N/A

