In addition, to avoid any possibility of the treatment allocation becoming too predictable, we will include a random factor within the algorithm in which for a proportion of the allocations (1 in 5) true randomisation will be implemented rather than by using the minimised allocation.]

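### The amenorrhoea and heavy-bleeding proportions are assigned a chi-squared test with no covariates, although allocation is minimised on six variables and the continuous outcomes are adjusted for them

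*Protocol*

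**What the plan says.** **Allocation (Protocol 5.6.1).** "A minimisation procedure using a computer based algorithm will be used to avoid chance imbalances in treatment allocation" and in six variables: age, BMI, any fibroid >2 cm, duration of symptoms, site, and agreement to enter the sub-study. There is a random element: "for a proportion of the allocations (1 in 5) true randomisation will be implemented".

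**Continuous outcomes (9.2.1 and 9.2.2).** For the primary MMAS model, "Baseline score and the minimisation variables (listed in section 5.5.1) will be included in the model as covariates". (The list now stands in 5.6.1; the cross-reference was not updated.) The other continuous measures "will be analysed in a similar fashion to the MMAS scores", that is, adjusted.

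**Bleeding-diary categories (9.2.2).** These include amenorrhoea (score 0) and heavy bleeding (score 100 or more). "They will be analysed using relative risks and chi-squared tests". No model and no covariates are named.

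**Likert and satisfaction outcomes (9.2.2).** These "will be analysed using standard methods (tests for trend, absolute and relative risks"). Whether they are adjusted is not stated.

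**Sidedness (9.2).** "p-values from two-sided tests will be reported".

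**The concern.** Minimisation makes the arms more alike on the listed factors than simple randomisation would. If those factors predict bleeding, the true sampling variance of the difference in proportions is smaller than the variance a two-group chi-squared test assumes. The test is then too cautious: its real type I error falls below 5% and its power falls with it. An analysis that includes the factors restores both.

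The protocol follows this principle for every continuous outcome but names no adjustment for the diary proportions, and gives no reason for the difference. Menstrual blood loss is the first item in the comparative secondary objective (2.1.2), and the diary-based bleeding outcome is the first secondary outcome listed (2.2.2). What is at stake is precision on those results, and consistency between two families of outcomes in one trial.

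**Working it through.** **1. The plan's own figures.** The protocol gives a sample size for MMAS only, and no power for any binary or ordinal outcome. With 0.5 SD, two-sided 5% and 90% power:

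- n per group = 2 × (1.960 + 1.282)² / 0.5² = 84.1, rounded up to 85. The t-test version gives 85.03, rounded up to 86, as stated.
- Loss of 20%: 172 / 0.8 = 215, against 220 stated. The stated size is reproduced closely.
- Women expected in the analysis: 220 × 0.8 = 176, about 88 per arm.

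**2. Why minimisation matters to the chi-squared test.** The statistic is

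X² = (p₁ − p₀)² / [p̄(1 − p̄)(1/n₁ + 1/n₀)].

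The term p̄(1 − p̄) equals the average within-stratum variance plus the variance of risk between strata. Minimisation removes much of the between-strata part from the actual variability of p₁ − p₀, but the denominator still counts it. The excess is zero if the factors do not predict the outcome and grows as they predict it more strongly.

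**3. Simulation inputs.**

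- From the protocol: 220 women, 1:1, minimisation with 1 in 5 allocations random (favoured arm chosen with probability 0.8 + 0.2 × 0.5 = 0.9), 20% loss, two-sided 5%.
- Assumed, because the documents give no figures: control risk about 0.5; treatment log-odds 0.85, giving a risk of about 0.65-0.70 on treatment; four binary factors, each with the same odds ratio (OR); five equal sites with smaller effects; loss at random. The sub-study factor is omitted.
- ORs of 1.65, 2.7 and 4.5 are exp(0.5), exp(1.0) and exp(1.5).

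**4. Results, 10,000 trials per setting (%).** Adjusted tests are a linear risk-difference model with robust errors and a logistic likelihood-ratio test, both with the minimisation factors as covariates.

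| OR per factor | Type I: chi-squared | Type I: linear / logistic | Power: chi-squared | Power: linear / logistic | Loss (points) |
|---|---|---|---|---|---|
| 1.0 | 5.0 | 5.3 / 5.7 | 79.0 | 79.2 / 80.2 | 0.2 to 1.2 |
| 1.65 | 4.9 | 5.5 / 6.0 | 74.0 | 75.4 / 76.6 | 1.4 to 2.6 |
| 2.7 | 3.3 | 4.8 / 5.3 | 64.6 | 70.7 / 72.3 | 6.1 to 7.7 |
| 4.5 | 3.0 | 5.5 / 5.9 | 51.5 | 64.7 / 66.8 | 13.2 to 15.3 |

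The Monte Carlo standard error of a 5% rate is √(0.05 × 0.95 / 10,000) = 0.2 points. Compare within rows: for a fixed log-odds, the overall treatment effect shrinks as the factors strengthen, so the rows do not share one effect size.

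**5. Checks.**

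- The closed-form power for 0.5 against 0.7 with 86 per group is 76.8%, close to the simulated 79.0% with about 88 per group and no prognostic factors.
- At OR 2.7 with simple randomisation instead of minimisation, the chi-squared type I error was 5.2% (2,000 trials), against 3.8% with minimisation in a run of the same length. The deficit therefore comes from ignoring the minimisation.
- The model recommended below, Poisson with robust errors, was simulated separately with the same control risk and treatment effect. Type I error stayed near 5%, and power exceeded chi-squared by about 0, 2 and 6 points at ORs of 1.0, 1.65 and 2.7.

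**The case against.** **The protocol never says unadjusted.** In 9.2.1 a chi-squared test denotes the test of the treatment term in an adjusted regression, and a relative risk can come from an adjusted model. So 9.2.2 could be read the same way. This stands only in part. In 9.2.1 the test is expressly tied to a regression with listed covariates; 9.2.2 names no model for the diary categories, and its plain sense is a two-group test.

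**Covariates for secondary outcomes belong in the SAP.** A full plan is promised in 9.2, and silence alone would be no finding. But here the protocol names a method, and that method differs from the one it fixes for the continuous outcomes.

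**The loss is conditional.** This stands. Section 5.6.1 calls the variables only potentially important. A reader might infer that the intervals are certainly too wide and that real differences will be missed; the documents give no association between any factor and bleeding, and with weak factors the effect is negligible. The larger losses need every binary factor to have an OR of about 2.7 or more at once.

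**Part of the apparent gain is size.** This stands for the logistic test, whose type I error was 5.3-6.0%. The robust linear model at OR 2.7 has 4.8% and still gains 6 points.

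**The ordinal outcomes are different.** This stands. A reader might infer that Likert and satisfaction outcomes also get unadjusted chi-squared tests. Section 9.2.2 assigns them tests for trend with absolute and relative risks, and leaves adjustment unstated.

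**Baseline PBAC is not free to use.** This stands. Sections 5.2 and 5.4 show that a woman with no period between visits may have no baseline diary, and 8.1.2 uses a modified diary at follow-up.

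**Conclusion.** The concern holds in a limited form. For the diary proportions the protocol names a test that takes no account of the minimisation variables, while it adjusts the continuous outcomes for them. If those variables predict bleeding, the test is conservative. Under the assumptions above the loss of power is about 0-1 point with no association, 1-3 points at an OR of 1.65 per factor and 6-8 points at 2.7, with type I error then about 3-4%. Which setting applies cannot be told from the documents. The figures also refer to the planned 220 women; recruitment is suspended, and this version does not say how many were randomised.

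A reader might infer that the trial's conclusions are unsafe. They are not on this account: the primary MMAS analysis is adjusted, only secondary outcomes are touched, and the error is towards missed differences rather than false positives. The case for change is that adjustment costs almost nothing where the factors are weak and recovers useful power where they are strong.

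**What to change.** State in the SAP that the main analysis of the amenorrhoea and heavy-bleeding proportions is an adjusted relative risk and an adjusted risk difference with 95% intervals. Use a log-binomial model, or Poisson with robust errors if it does not converge, with the minimisation variables as covariates. Keep the chi-squared test as supportive. Say in advance how sparse levels of site and sub-study agreement will be pooled.

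Two optional additions:

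- Baseline PBAC may be added as a covariate for the diary outcomes, with a stated rule for women who have no baseline diary.
- For Likert and satisfaction outcomes, the same covariates can be used in an ordinal model for consistency. This clarifies what is unstated; it does not correct an error.

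The cost is SAP wording and a few lines of code. The minimisation variables must be entered before a woman can be randomised, so the main change needs no new data.
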